**Fig. 2 Fig2:**
[figure not shown]
Recruitment and baseline data collection

### Description of intervention and usual care

Intervention clusters will receive EPAT plus usual care which will commence following HCP training and run for a maximum of 12-weeks per participant. The EPAT intervention will include: a training module to support clinician education; a pain screening conducted by clinic nurse/clinician (step 1); a detailed pain assessment (step 2) conducted by a physician or clinical nurse specialist for patients with a pain screen ≥ 3/10 on a 0–10 NRS of worst pain in past 72 h; a basic pain management algorithm/protocol to guide analgesic prescribing and/or onward referral to a pain specialist; and, patient resources to support self-management. EPAT will be in paper form, attached to the front of patient’s notes and implemented within existing policy. All patients with cancer (including those not recruited to the trial) attending intervention clusters that have a pain score of ≥ 3/10 will receive the intervention.

At least one HCP from each intervention cluster will take on the role of ‘EPAT champion’ to lead local implementation of the intervention, following training, with support from the trial team. Intervention champions will: have oversight of the relevant outpatient service; have direct interaction with patients and their medical notes; and have direct contact with clinical staff responsible for pain management. Oncologists and oncology nurses working in the cluster will be trained to deliver the intervention by the EPAT champion prior to the start of participant recruitment to ensure the intervention is established as routine practice. Champions will be supported by the research team via weekly catch-up calls and monthly video-call conferences with champions at other services to create a community of practice that will enable knowledge sharing. Data to support exploration of fidelity of intervention delivery will be collected. EPAT will not be available for clusters randomised to deliver usual care alone.

Participants in all clusters, including those randomised to receive EPAT, will receive usual care. It is anticipated that usual care will consist of appropriate individual pain assessment by nursing and medical staff, followed by a management decision. At present in the UK, this part of cancer care is not carried out in a structured, systematic fashion. While pharmacological management is based on the principles of WHO guidelines, the way in which these guidelines are used is not standardised. Pain management provided will be recorded and data describing usual care provision will be collected.

### Outcomes and data collection

The primary outcomes for this trial are the eligibility, recruitment, retention, and follow-up rates. Secondary outcomes include acceptability, intervention fidelity, feasibility of economic evaluation, pain, quality of life, psychological health, and common symptoms.

Baseline data collection will include participant identifiers, demographics (ethnicity, marital status, employment, and education), cancer-specific details (cancer type and stage and date of diagnosis) and pain-specific details (primary cancer site causing pain, clinical diagnosis of pain and analgesic prescribing) (Table 1).

**Table 1 Tab1:** Description of outcome and process measures, including their timing and method of data collection

Assessment	Measure	Method of completion	Screening	Baseline	1-week	1-month	2-months
**Recruitment processes**							
Screening	Screening form	RN (from clinic screening list)	X				
Contact details	Patient telephone number	RN (from medical records)	X	X			
Eligibility	Researchers will ask the patient if they have had any pain in the past 72-h	RN (from participant)	X	X			
Consent	Consent form	Participant	X	X			
Participant registration	CRF	RN	X	X			
**Pain**							
Pain	BPI	Participant self-report	X	X	X	X	X
**Health & Wellbeing**							
General health-related Quality of life	5Q-5D-5L	Participant Self-report		X	X	X	X
Anxiety	GAD-7	Participant Self-report		X		X	X
Depression	PHQ-8	Participant Self-report		X		X	X
Symptoms	EASA	Participant Self-report		X		X	X
**Participant characteristics**							
Demographics	Basic demographics: age, ethnicity, marital status, sex, highest achieved education level	RN (from participant)		X			
Medical history	Recent medical history, cancer type and stage	RN (from participant)		X			
Medications and referral check plus healthcare resource use	Analgesic prescriptions, specialist service referral, healthcare resource use	RN (from medical records)		X		X	X
Healthcare resource use	specialist service referral, healthcare resource use	Participant self-report		X		X	X
**Other**							
Usual care	Site level usual care offered and accessed	Participant interviewed about use of usual care during process evaluation					X
Intervention training	Evidence of intervention training delivered to clinic staff by intervention champion recorded on CRF	Researcher at University of Leeds		X			
Intervention delivery and fidelity	Completion of EPAT forms by outpatient clinical staff, evidence of EPAT completion recorded on CRF by research nurse for all participants (who consented to provide outcome data) at one-month and two-month follow-up time points	Researcher at University of Leeds				X	X

Participants will be asked to complete participant reported outcome measures at baseline, 1 week, and 1- and 2-months post randomisation. At baseline, measures can be completed over the telephone with a research nurse or in-person prior to a participant’s outpatient appointment. Follow-up data will be collected by post or via an online platform (REDCap) supplemented by reminders including telephone, and SMS prompts (Fig. 3).

**Fig. 3 Fig3:**
[figure not shown]
Follow-up data collection

Participant reported outcome measures include:

*Pain:* The short form Brief Pain Inventory (BPI) [26] is a 9-item tool to assess the severity of pain and its impact on daily function.

*Quality of Life: EQ-5D-5L *[27] is a 5-item generic health related QoL measure.

*Psychological Health:* The Generalised Anxiety Disorder 7-item Scale (GAD-7) [28] is a seven-item measure of anxiety. The Patient Health Questionnaire (PHQ-8) [29] is an eight-item measure of depression.

*Common Symptoms:* The Edmonton Symptom Assessment System (EASA) [30] is a ten-item tool designed to assess common symptoms in palliative care patients.

*Resource Use:* The Health Service Use Questionnaire (HSUQ) is a brief, bespoke questionnaire designed to capture patients’ health services use across 5 key areas: hospital services, out-of-hours services, hospice services, travel to and from services, and support from family and friends.

### Safety

In this population it is anticipated that participants will experience acute illnesses, infection, new medical problems, and deterioration of existing medical problems. This could result in hospitalisation, hospital re-admission, disability, incapacity, or death. Therefore, any events fulfilling the definition of an Adverse Event (AE) or Serious Adverse Event (SAE) will not be reported unless they fulfil the definition of a reportable event or a Related and Unexpected Serious Adverse Event (RUSAE).

SAEs and RUSAEs will be monitored and assessed through case report forms (CRFs), contact with the research team/principal investigator at site, research team at the University of Leeds and via follow-up questionnaires. If either research team becomes aware that a trial participant that has died, a CRF will be completed to capture the event. As this is expected within this population, it will not be subject to expedited reporting to the main Research Ethics Committee (REC).

Reportable events include RUSAEs, hospitalisations that have been associated with uncontrolled pain (inpatient stays and A&E attendances), contacting out of hours services and Clinical Nurse Specialist (CNS) for uncontrolled pain. Hospitalisations (except for those associated with uncontrolled pain) are expected within this population and will not be subject to expedited reporting.

### Sample size

A formal power calculation is not required for this pilot trial, as it is not designed to estimate effectiveness. However, the sample size must be sufficient to establish eligibility, consent, recruitment, and dropout rates and assess the acceptability and fidelity of EPAT to inform a future trial. Teare et al. [31] recommends a minimum of 60 participants per arm for a pilot trial with a binary primary outcome variable. Allowing for 30% loss to follow-up and rounding to allow balanced recruitment across clusters, a total sample size of 180 participants (90 participants per arm; 15 patients per cluster) will be sufficient [32, 33].

### Analysis

A detailed statistical analysis plan will be written and signed off before any analysis is undertaken. The analysis will focus on descriptive statistics and confidence interval estimation. All analyses will be conducted on the intention-to-treat population, in which all participants will be included in the analysis according to the randomised allocation of the service they were recruited from, and regardless of non-adherence with the intervention or withdrawal from the trial. Final analysis will be conducted when all available outcome data has been received. All summaries will be presented overall, by arm and by cluster (where relevant) using frequencies and summary statistics. The number of participants with missing data will be presented. All participant reported outcome measures will be scored according to relevant scoring manuals and summarised overall, and by arm at each time-point. Point estimates and 95% confidence intervals for the difference in outcomes between arms will be presented. No inferential testing is planned.

The primary outcome for the definitive trial is pain intensity as measured by the BPI; a ≥ 2 point reduction between baseline and 1-week follow-up would be considered a clinically significant change in pain intensity. [34] To generate evidence of proof of principle, the mean change from baseline in the 1-week, 1-month and 2-months BPI scores in the two arms will be reported, together with a range of confidence intervals around the main estimate to inform us as to the likelihood of where the ‘true’ estimate may lie. Analysis will adjust for the minimisation factors.

This trial is not powered to provide a precise estimate of the levels of clustering relating to intervention group effects but it will allow an investigation of this effect [35]. We will estimate the Intra-cluster correlation coefficient (ICC) and produce a range of confidence intervals around this to inform the sample size of the definitive trial.

Pre-defined progression criteria (Table 2) will be used to judge whether it is feasible to progress to a larger definitive trial. While these are the main considerations for the decision to progress to a definitive phase III trial, we will also consider data from all primary and secondary endpoints, and any issues related to successful trial delivery, to determine the feasibility of progressing.

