### Setting, clusters, and randomisation

Oncology outpatient services will be eligible for inclusion if they:Care for patients with a diagnosis of cancer.Do not currently have a standardised pain assessment and management programme integrated within routine practice.Provide written informed consent to support participation.

Each site will be required to have obtained local trust approvals and have undertaken a site initiation meeting within the trial team before services are randomised and participant recruitment starts. Following confirmation of eligibility, services will be randomised (1:1) to deliver EPAT plus usual care or usual care alone (Fig. 1) by the trial statisticians (MC, SG) at the Leeds Clinical Trials Research Unit (CTRU). Minimisation, incorporating a random element will be undertaken by hand to ensure treatment arms are balanced with respect to site, cancer type (i.e., breast vs. lung vs. prostate vs. bowel vs. upper GI vs. haematology vs. bone metastasis) and pain prevalence (high vs. low).

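### The BPI comparison names only service-level factors for adjustment; it should also state adjustment for each participant's baseline BPI

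*Protocol article*

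**What the plan says.** The Analysis section of the protocol article states that "The primary outcome for the definitive trial is pain intensity as measured by the BPI", and that a 2-point "point reduction between baseline and 1-week follow-up would be considered a clinically significant change in pain intensity". For proof of principle, "the mean change from baseline in the 1-week, 1-month and 2-months BPI scores in the two arms will be reported", with a range of confidence intervals around the main estimate. The same paragraph ends: "Analysis will adjust for the minimisation factors".

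The section on setting, clusters and randomisation lists those factors. Minimisation is meant to "ensure treatment arms are balanced with respect to site, cancer type" and service pain prevalence (high or low). Each is a property of the service, not of the participant.

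Table 1 lists the BPI as "Participant self-report" at screening, baseline, 1 week, 1 month and 2 months, so an individual baseline score is available. The Analysis section does not name it as a covariate and does not rule it out. It defers detail to a statistical analysis plan that is not shown. It also says that an ICC will be estimated to inform the size of the definitive trial, without saying from which model.

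**The concern.** The text chooses a form for the outcome (change) and names what to adjust for (service-level factors). On that reading, a participant's baseline score is used only by subtracting it, which fixes its slope at 1. Pain scores fluctuate, so the true slope is likely to be below 1. Two things follow: some of the precision available from data already collected is lost, and any difference in baseline pain between arms is over-corrected.

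Such a difference is plausible here. Only 12 services are randomised. Participants are recruited afterwards by research nurses who know the allocation (section on protecting against bias), and the Discussion itself acknowledges possible selection bias from this order of events.

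At stake are the centre and width of the proof-of-principle intervals, and the variability figures carried forward to the definitive trial.

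**Working it through.** **The plan's own figure.** 60 / (1 - 0.30) = 85.7, so 86 per arm. 86 / 6 services = 14.3, so 15 per service. 15 x 6 = 90 per arm and 2 x 90 = 180. This matches the Sample size section. No BPI quantity enters, so nothing below changes it.

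**Inputs.** From the protocol: 6 services and 90 participants per arm; 30% loss, leaving 90 x 0.7 = 63 per arm, or 10.5 per service; entry at worst pain of 3 or more. Assumed, because the document gives no values: correlation r between baseline and follow-up of 0.3 to 0.8, SD 2.5, ICC 0 or 0.05.

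**Precision.** With equal SDs at both times and in units of SD squared, the variance is V = 2(1 - r) for change and V = 1 - r^2 after baseline adjustment. The ratio is (1 + r)/2. The 95% half-width is 1.96 x SD x sqrt(V x (2/63) x DE), with DE = 1 + 9.5 x ICC, which is 1 or 1.475. Example at r = 0.5 and ICC 0: 1.96 x 2.5 x sqrt(1.00 x 2/63) = 0.87 for change, and 0.76 with V = 0.75.

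| r | V change | V adjusted | ratio | interval narrower by | half-width, ICC 0 | half-width, ICC 0.05 |
|---|---|---|---|---|---|---|
| 0.3 | 1.40 | 0.91 | 0.65 | 19% | 1.03 to 0.83 | 1.25 to 1.01 |
| 0.5 | 1.00 | 0.75 | 0.75 | 13% | 0.87 to 0.76 | 1.06 to 0.92 |
| 0.7 | 0.60 | 0.51 | 0.85 | 8% | 0.68 to 0.62 | 0.82 to 0.76 |
| 0.8 | 0.40 | 0.36 | 0.90 | 5% | 0.55 to 0.52 | 0.67 to 0.64 |

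The same ICC is used for both analyses in a row. A t-value suited to 12 clusters would widen both equally.

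**Baseline imbalance.** With no treatment effect, and follow-up depending on baseline in the same way in both arms, an imbalance D gives an expected change-score difference of -(1 - r)D. For D = 1 this is -0.70, -0.50 and -0.30 at r = 0.3, 0.5 and 0.7; for D = 0.5 it is half of that.

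**Regression to the mean.** This was simulated with no treatment effect, entry cut at 3, SD 2.5 and slope 0.5.
- Equal baselines: both arms fell by about 0.45 points, and the arm difference was about 0.
- Baseline means of 5.92 and 6.55: the arms fell by 0.46 and 0.77. The change-score difference was -0.31 (formula: -0.5 x 0.63 = -0.315) and the baseline-adjusted difference was 0.00.

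In the equal-baseline run the residual variance was 5.58 for change and 4.69 after adjustment, a ratio of 0.84 rather than 0.75. The entry cut narrows the spread of baseline scores, so the equal-SD figures are somewhat generous.

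**Residual SD.** Change relative to adjusted is sqrt(2/(1 + r)) = 1.24, 1.15 and 1.08 at r = 0.3, 0.5 and 0.7.

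**ICC.** Take ICC 0.05 at each time, within-service correlation 0.5 and slope 0.5.
- Service-level correlation 0.9: change gives 0.01/(0.01 + 0.95) = 0.010; adjusted gives 0.0175/(0.0175 + 0.7125) = 0.024.
- Service-level correlation 0: change gives 0.10/(0.10 + 0.95) = 0.095; adjusted gives 0.0625/(0.0625 + 0.7125) = 0.081.

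The order reverses, so the direction is not fixed.

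**The case against.** The strongest reply is that the document never says baseline BPI is left out. It names some adjustment factors without calling the list complete, and it defers to a SAP. A model for change with baseline as a covariate would be consistent with the text and would give the same arm estimate as adjusting the follow-up score. Reporting mean change by arm is also a legitimate description. This stands as a limit on confidence: a reader might infer that the trial will be analysed without baseline BPI, and the article does not establish that. The point survives because the article does state an outcome form and an adjustment set, and following those as written has the costs shown.

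A second reply is that little depends on this. The article says "A formal power calculation is not required for this pilot trial, as it is not designed to estimate effectiveness" and "No inferential testing is planned". That is right for the sample size and the feasibility outcomes. It does not dispose of the point, because interval estimation is the stated focus of the analysis and estimating variability in outcomes is among the stated aims.

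Third, service pain prevalence is a minimisation factor and a rough proxy for baseline pain, so the comparison is not wholly unadjusted for it. That is true, but a two-level service factor cannot stand in for a participant's own score.

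Fourth, baseline adjustment is not a complete cure. Under the section describing the intervention, EPAT is in use before recruitment begins and is given to every patient in those services who scores 3 or more, so baseline scores of returning patients may already reflect it. Selection on unmeasured factors also remains. If an imbalance reflects stable differences between services, the relevant slope may be nearer 1 and the change-score shift smaller than shown.

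**Conclusion.** The point holds in a limited form. Followed as written, the BPI arm difference is less precise than a baseline-adjusted one and over-corrects any baseline imbalance. The sizes rest on assumed correlations, equal SDs and a common relation of follow-up to baseline in both arms. The entry threshold makes the precision gain smaller: in the simulation, 16% of variance instead of 25%.

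Three stronger readings are not supported:
- Regression to the mean is not a separate bias in the arm difference. The entry threshold applies to both arms and its effect cancels when baselines match. It reaches the difference only through imbalance, although it does affect each arm's own reported mean change.
- Change scores do not inflate every planning quantity. Only the residual SD is predictably larger; the ICC and the arm difference can move either way. The Analysis section names only the ICC as informing the definitive trial's size.
- Nothing here calls the 180 participants or the feasibility outcomes into question.

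It is worth correcting because the data exist and the change is small, not because the pilot is invalid without it.

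**What to change.** In the Analysis section, or by confirming that the SAP already does so, state that the between-arm difference in BPI at 1 week, 1 month and 2 months is estimated from a model that adjusts for individual baseline BPI as well as the minimisation factors and accounts for cluster. State also that the residual SD and ICC used to plan the definitive trial are reported from that model.

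Keep mean change per arm as a descriptive summary. Tabulate baseline BPI by arm, because it is measured after allocation and may already reflect EPAT; a marked difference should temper how the adjusted estimate is read.

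The cost is a few sentences of protocol or SAP wording before analysis. No new data, participants or visits are needed.

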## Methods

### Trial design

We will use a multi-centre, two-arm, pilot cluster randomised controlled trial, with a nested qualitative process evaluation. Twelve outpatient services (clusters) from at least two NHS tertiary oncology referral centres (sites) in the North of England will be randomly allocated (1:1) to deliver EPAT + usual care or usual care alone. 180 eligible patients will be recruited.

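### Adjusting the BPI comparison for every minimisation factor, including a seven-level cancer type, leaves about 2 between-cluster degrees of freedom from 12 services

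*Protocol article*

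**What the plan says.** The Analysis section of the protocol article closes its paragraph on change in BPI score with an unqualified rule: "Analysis will adjust for the minimisation factors". The section on setting, clusters and randomisation names the factors: site, pain prevalence in two levels, and cancer type in seven ("breast vs. lung vs. prostate vs. bowel vs. upper GI vs. haematology vs. bone metastasis"). Services are what is minimised, so all three factors are properties of the service. The Trial design section fixes twelve services "from at least two NHS tertiary oncology referral centres (sites) in the North of England".

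The paragraph after the BPI one turns to clustering: "We will estimate the Intra-cluster correlation coefficient (ICC) and produce a range of confidence intervals". It does not say which model yields the ICC, and it disclaims a precise estimate of clustering. The article also promises a detailed statistical analysis plan, plans no inferential testing, and makes descriptive statistics and interval estimation the focus.

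**The concern.** In a cluster trial, cluster-level covariates are paid for out of the number of clusters, not the number of participants. Seven cancer types across 12 services is close to one indicator per service, and site, prevalence and arm come on top. Little is then left from which to estimate between-service variation or to compare arms.

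At stake is the adjusted arm difference in BPI. The protocol wants its intervals to show where the true effect may lie, and it treats a reduction of 2 points as clinically significant. If the stated model is fitted with proper degrees of freedom, the interval may be too wide to say much against that yardstick. If it is fitted without a small-sample correction, the interval may be too narrow.

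**Working it through.** **Inputs from the protocol.** 12 clusters, 6 per arm; at least 2 sites; 7 cancer types; 2 prevalence levels; 15 participants per cluster; 30% loss to follow-up, so 15 × 0.7 = 10.5 analysed per cluster.

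**The plan's own figure.** 60 / 0.70 = 85.7, so 86 per arm; 86 / 6 = 14.3, rounded up to 15 per cluster; 15 × 12 = 180. This agrees with "a total sample size of 180 participants (90 participants per arm; 15 patients per cluster) will be sufficient". The adjustment rule does not bear on it.

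**Degrees of freedom.** With S sites and C cancer types represented, between-cluster df = 12 − 1 (intercept) − 1 (arm) − (S − 1) − (C − 1) − 1 (prevalence). For S = 2 and C = 7 this is 12 − 1 − 1 − 1 − 6 − 1 = 2.

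| Sites | 7 types | 6 types | 5 types |
|---|---|---|---|
| 2 | 2 | 3 | 4 |
| 3 | 1 | 2 | 3 |
| 4 | 0 | 1 | 2 |

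Arm alone leaves 10 df. Arm, site and prevalence with two sites leave 8. The 95% t multipliers are 2.23 (10 df), 2.31 (8 df), 4.30 (2 df) and 12.71 (1 df). Going from 10 to 2 df widens the interval by 4.30 / 2.23 = 1.93 before anything else.

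**Services that stop contributing.** If s of the seven types have one service each, 12 ≥ s + 2(7 − s), so s ≥ 2. A lone service is fitted exactly by its own type indicator. At least 2 × 15 = 30 of the 180 participants therefore add nothing to the adjusted arm contrast.

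**Variance inflation of the arm contrast.** These figures come from simulated allocations with two sites and all seven types present, at equal residual variance.
- Layouts close to minimal imbalance: median inflation 1.85 (10th to 90th percentile 1.3 to 3.0). The interval widens by 1.93 × √1.85 ≈ 2.6.
- Minimisation with an 80% biased coin: median widening 3.1 (10th to 90th percentile 2.4 to 4.7). A median of 7 of 12 services lie in a type present in both arms.
- Site plus prevalence only: 1.06, so cancer type is the cause.
- Fewer types represented, two sites: about 2.0 with six, 1.6 with five.
- Three sites and all seven types: about 11, and in about 7% of runs the adjusted arm effect cannot be estimated.

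**On the BPI scale.** The protocol gives neither an SD nor an ICC. I assume SD 2.0 to 2.5 and ICC 0.01 to 0.10. Half-width = t × SD × √[(ICC + (1 − ICC)/10.5) × 4/12]. For SD 2.0 and ICC 0.05 the standard error is 2 × √(0.1405/3) = 0.433. The first three columns below use the t multiplier alone; the last also applies √1.85.

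| Assumptions | Arm only (10 df) | Site + prevalence (8 df) | All factors (2 df), t only | All factors, median inflation |
|---|---|---|---|---|
| SD 2.0, ICC 0.05 | 0.96 | 1.00 | 1.86 | 2.53 |
| Whole range | 0.8 to 1.4 | 0.9 to 1.4 | 1.6 to 2.7 | 2.2 to 3.6 |

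**The ICC, only if taken from the fully adjusted model.** For an estimate of 0.05, F = (1 + 9.5 × 0.05)/0.95 = 1.55 with within-cluster df 12 × 10.5 − 12 = 114. The F-based 95% interval is −0.03 to 0.27 on 10 df and −0.06 to 0.85 on 2 df. If the true ICC is 0.05, the chance of an estimate at or below zero rises from 23% to 47%. The same instability explains how a mixed model could give intervals that are too narrow: when the cluster variance is set to zero, participants are treated as independent.

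**The case against.** The strongest reply is that this is a feasibility pilot. Its primary outcomes are eligibility, recruitment, retention and follow-up rates, BPI is secondary, no test is planned, and a detailed analysis plan is to follow. That stands as to severity. It does not remove the point, because the rule is stated without limit. An analysis plan that follows it inherits the problem, and one that drops or collapses cancer type departs from the protocol.

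The figures also depend on layout. The protocol lists seven categories but does not say that all will be recruited; with five types the widening is about 1.6. More than two sites, which the protocol allows, makes it worse.

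The width ratios give no credit for between-service variation that the covariates may explain. At ICC 0.05, if they explained all of it, width would fall by the factor √(0.0905/0.1405) = 0.80. Then 2.6 to 3.1 becomes about 2.1 to 2.5, which is smaller but still large.

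A reader might infer that the ICC is ruined as well. The documents do not support this. The adjustment sentence belongs to the BPI paragraph and no model is named for the ICC. An arm-only or unadjusted ICC keeps 10 or 11 df. Nor does spending degrees of freedom in itself remove between-service variation: with a df-corrected estimator the variance is estimated less precisely, but without bias before truncation at zero. Even on 10 df the ICC is imprecise, as the protocol concedes.

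**Conclusion.** The point holds for the adjusted BPI comparison. With two sites and all seven cancer types represented, the stated model leaves 2 between-cluster df. At equal residual variance the interval is then about 2.6 to 3.1 times as wide as with arm alone. Under the assumed SD and ICC, that is a half-width of about 2.2 to 3.6 points against a clinically significant change of 2. Site plus prevalence costs almost nothing.

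It would go too far to call such an interval wrong. On correct degrees of freedom it has proper coverage and is simply uninformative. The opposite error, an interval that is too narrow, arises only if no small-sample correction is used, and the article names no method either way. Any effect on the ICC is conditional on using the same model, and is a loss of precision.

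This should be fixed before analysis. It does not undermine the trial: the feasibility outcomes and the 180 participants are untouched.

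**What to change.** Replace the adjustment sentence with one to this effect: *the BPI model will adjust for site and pain prevalence; cancer type will be omitted, or collapsed to very few groups specified in advance, and outcomes by cancer type will otherwise be described only.* Add that intervals will use a small-sample method, such as Kenward-Roger or a cluster-level t on 12 minus the number of cluster-level parameters. State that the ICC will be estimated from a model without the seven-level cancer type.

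The cost is a sentence or two, settled before outcome data are examined. The downside is that one minimisation factor goes unadjusted, or is adjusted only coarsely, so intervals may be slightly conservative. The change will not make the ICC precise: at an estimate of 0.05 its upper limit stays near 0.27 on 10 df.
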